### Outcomes

#### Primary outcome

Identification of pneumoclusters among patients with suspected VAP using unsupervised consensus clustering of BAL proteomic data alone and in combination with clinical and microbiological variables.

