### Sample size

As an exploratory clustering study, a formal power calculation is not applicable. Based on anticipated heterogeneity and the expectation of four to six major clusters, the target sample size is 400 patients. This number balances scientific aims with the resource-intensive nature of proteomic analysis and is considered sufficient to identify clinically meaningful clusters while allowing for internal validation.

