### Statistical analysis

Proteome-driven unsupervised consensus clustering will be used to discover pneumoclusters that are then described using clinical, microbiological and radiological features. Proteomic data processing will include analysing raw DIA files (dia-PASEF on Bruker timsTOF) with DIA-NN (V.1.8.1) against the UniProt human reference proteome. False discovery rate (FDR) will be controlled at 1% at both precursor and protein levels using a target–decoy strategy. Proteins with >70% missing values across all samples will be removed. Retention-time–dependent normalisation followed by median normalisation will be applied.

Unsupervised consensus clustering with resampling will be applied to define stable clusters, with cluster number determined by cumulative distribution function and silhouette width. Differential abundance will be assessed using limma. Multiple testing will be controlled with Benjamini-Hochberg correction and proteins will be considered significant at adjusted p<0.05 and |log₂ fold-change|>1.5. Gene set enrichment will be performed using clusterProfiler against Gene Ontology and Reactome collections with FDR<0.01.

30-day outcomes, including mortality and days free of ventilation, intensive care, hospitalisation and antibiotics, will be compared across clusters to characterise distinct clinical trajectories. Missing proteomic data will lead to exclusion from clustering; missing clinical variables will be handled by complete case analysis for relevant comparisons.

Candidate protein biomarkers that enable pragmatic assignment to clusters will be derived using differential expression methods and feature selection methods, with the intention of informing future validation with receiver operating characteristic (ROC) curves in separate patient cohorts and, ultimately, clinical application. Biomarker validation is planned in an independent external prospective observational study (VAPmarkers; ClinicalTrials.gov: NCT05117125). Validation will rely on targeted quantification of selected proteins using ELISA or equivalent immunoassays, and diagnostic and prognostic performance will be assessed using ROC curves.

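### Proteins are tested between clusters built from those same proteins, so the stated multiple-testing control is not guaranteed and the results should be presented as a descriptive ranking

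*Protocol article*

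**What the plan says.** Under Primary outcome, the Protocol article defines the clusters by "unsupervised consensus clustering of BAL proteomic data alone and in combination with clinical and microbiological variables". The proteome is therefore an input in both variants. Statistical analysis adds: "Unsupervised consensus clustering with resampling will be applied to define stable clusters, with cluster number determined by cumulative distribution function and silhouette width".

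The next steps in the same section are "Differential abundance will be assessed using limma" and then the decision rule: "Multiple testing will be controlled with Benjamini-Hochberg correction and proteins will be considered significant at adjusted p<0.05", with the further condition of an absolute log2 fold-change above 1.5. Both conditions must be met. Gene-set enrichment follows, at a false-discovery rate below 0.01.

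The tests serve to find markers of cluster membership: "Candidate protein biomarkers that enable pragmatic assignment to clusters will be derived using differential expression methods and feature selection methods". The contrast is thus between the derived clusters.

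Sample size gives "the expectation of four to six major clusters, the target sample size is 400 patients", which is "considered sufficient to identify clinically meaningful clusters while allowing for internal validation". The article does not say what the internal validation consists of. Accuracy of the selected proteins is to be assessed in VAPmarkers, an independent cohort, by immunoassay and ROC curves.

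**The concern.** Clustering groups patients so that their proteomes differ between groups. A test of those same proteins, in those same patients, between those groups then asks a question whose answer was partly fixed when the groups were formed. A p-value is valid only if the labels do not depend on the tested data under the null, and here they do. Benjamini-Hochberg takes p-values as input and cannot repair them.

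No separate data, null calibration or selective-inference step is tied to the tests. The sensitivity analyses do not separate the data either: the first repeats clustering and testing together on the same samples, and the others change the sample set or look at freezing time.

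At stake is an error rate that the paper would report without having it. If patients lie along a continuum rather than in discrete groups, proteins could still be declared significant, and immunoassay targets would be drawn from that list. Gene-set enrichment based on these contrasts is open to the same concern, though this was not simulated.

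**Working it through.** **Inputs from the Protocol article.** N = 400; 4 to 6 clusters, hence 400/6 ≈ 67 to 400/4 = 100 patients per cluster if equal; consensus clustering with resampling; adjusted p<0.05 and absolute log2 fold-change above 1.5.

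**Assumptions not in the article.** 1000 proteins; protein SD 1 to 2 log2 units; 10 continuous latent factors, each shared by 100 proteins and carrying a share r of their variance, r = 0 to 0.6.

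**Model with no clusters.** X_ij = SD × (√r × F_i,b(j) + √(1−r) × e_ij), with F and e independent standard normal and b(j) the factor on which protein j loads.

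**Analysis.** Consensus k-means with 80% resampling (plain k-means when r = 0); one-vs-rest t-tests per protein in place of limma; Benjamini-Hochberg within each contrast, q_(i) = min over l ≥ i of 1000 × p_(l)/l; a protein is declared if any contrast passes. Fold-change is the difference of group means on the log2 scale.

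**Step 1: the intended behaviour.** With permuted labels, which are independent of the proteins, adjusted p<0.05 declares 0 to 1% of proteins. The procedure works when the labels do not depend on the data.

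**Step 2: labels from the same proteins, no true clusters, k = 5, eight data sets per cell.** Share of proteins declared:

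| r | adjusted p<0.05 (SD 1 to 2) | both conditions, SD 1 | both, SD 1.5 | both, SD 2 |
|---|---|---|---|---|
| 0 | 0.2-0.3% | 0% | 0% | 0% |
| 0.1 | 28% | 0% | 0.1% | 0.5% |
| 0.3 | 87-89% | 0% | 0.2% | 10% |
| 0.6 | 96-97% | 0% | 7% | 40% |

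The adjusted p-value hardly changes with SD because the t statistic is scale-free. The fold-change grows in proportion to SD while the 1.5 cut is fixed, so the protection given by the second condition depends on protein spread. At k = 6, SD 2 and r = 0.6 the two-part rule declared 48%.

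Other null simulations at k = 5 agree in direction. One gave adjusted p<0.05 for 4% of independent proteins and 65-99% at r = 0.1 to 0.6, with the two-part rule at 0% (SD 1), 0-17% (SD 1.5) and 0-57% (SD 2). Another, with six factors and plain k-means, gave 0-4% at SD 1 and 25-61% at SD 2 for the two-part rule.

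**Step 3: some real clusters (k = 5, SD 1.5, four data sets per row).** Cluster means of the shifted proteins are drawn with the SD shown. False share among declared proteins:

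| Shifted proteins, SD of shift | r | adjusted p, derived labels | both conditions, derived labels | adjusted p, true labels |
|---|---|---|---|---|
| 20, 0.5 | 0.3 | 98% | 25% | 7% |
| 100, 0.5 | 0.6 | 90% | 92% | 8% |
| 100, 1 | 0.3 | 90% | 37% | 11% |
| 300, 1 | 0 | 10% | 0% | 10% |
| 300, 1 | 0.3 | 10% | 0% | 8% |
| 300, 1 | 0.6 | 70% | 51% | 14% |

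The true-label column exceeds 5% because declarations are pooled over five contrasts, so it is the fair baseline. Where the real groups dominate (300 proteins, r up to 0.3), derived labels do about as well as true ones. Where shared continuous variation dominates, they do not.

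**Step 4: would a simple split help?** Clustering one half, assigning the other half to the nearest centre and testing there still gave adjusted p<0.05 for 4 to 88% of proteins at r = 0.1 to 0.6, because the held-out patients are assigned with the proteins under test. Gaussian data thinning with known covariance, which clusters on one independent part and tests on the other, declared 0 to 0.3%.

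**The case against.** The best defence has four parts.

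- **The rule has two conditions.** Quoting adjusted p<0.05 alone would misstate the plan, and the fold-change cut removes many false calls. This stands: the size must be judged on the joint rule, which can be near 0%. But the protection varies with protein spread and is not tied to the 5% level.
- **The study is exploratory, the markers are candidates, and validation is external.** Patients in VAPmarkers are excluded from ClusterVAP to keep that cohort independent, and ROC performance is reserved for separate cohorts. This limits the harm and lowers the severity. It does not make this study's adjusted p-values valid, nor does it reach proteins that are not taken forward.
- **Differential abundance is not used to show that clusters exist.** Correct: cluster number rests on the consensus distribution function and silhouette width. But silhouette width is undefined for a single cluster, so it cannot return the answer of no subgroups, and whether distinct groups exist is the primary question.
- **Internal validation is named.** Its detail may sit in a fuller document and its absence here is no fault. A simple patient split would not cure the problem, though.

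Several stronger readings are tempting but unsupported. A reader might infer that there is no false-discovery control at all, or that p-values are far too small whether or not subgroups exist; Step 3 contradicts both when clusters are well separated, and independent proteins show almost no inflation. A reader might call every declared protein an artefact; yet proteins loading on a shared factor do mark a real axis of variation, and what fails is the claim of discrete groups. Nor does the article say that the panel is derived on all patients, or claim marker accuracy from ClusterVAP itself, so it cannot be faulted for an optimistic accuracy figure.

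**Conclusion.** The concern holds in a limited form. For contrasts between proteome-derived clusters, the p-values are not valid under the null of no distinct subgroups, and the statement that multiple testing will be controlled is not justified.

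The direction follows from the order of the steps; the size rests on assumed protein number, SD and correlation. With no true clusters, the full two-part rule flags from 0% of proteins to roughly 40-60% at SD 2 with strong shared variation, and the inflation nearly vanishes when clusters are real and well separated. The 30-day outcome comparisons are unaffected where outcomes are not clustering inputs, and the identification of clusters does not depend on these p-values. Because the tests serve a secondary outcome of an exploratory study, this is a should-fix and not a must-fix.

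**What to change.** In Statistical analysis:

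1. For proteins used in clustering, remove the claim of false-discovery control and the label significant. Report limma log2 fold-changes as a descriptive ranking, with each protein's selection frequency over resamples.
2. If a false-discovery rate is to be quoted, calibrate it by running the whole sequence, clustering plus limma, on simulated one-population data with the observed covariance. Data thinning or selective inference are alternatives; the thinning result above assumed a known covariance, which would have to be estimated in practice.
3. If held-out assignment accuracy is reported for the panel, repeat clustering and selection inside each training fold and compare the figure with the same figure from the one-population null, not with chance. In a check with no clusters and k = 5, panels of 28-30 proteins reached 64-86% held-out accuracy against chance of about 1/5 = 20%, so a comparison with chance would look reassuring when nothing is there.

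The cost is wording and computing time, with no new data. Repeating the clustering in folds also requires matching cluster labels between folds. The downside is a less impressive protein list.

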## Ethics and dissemination

Ethical approval will be obtained from the relevant research ethics committees or institutional review boards at all participating sites before study initiation. The Swedish Ethical Review Authority has approved the study protocol (Dnr 2025-04564-01) including waived consent. The study will be conducted in accordance with the principles of the Declaration of Helsinki and applicable national regulations governing research involving human participants.

The results of the study will be disseminated through publication in peer-reviewed journals and presentation at national and international scientific meetings. Statistical code and study protocol will be made available alongside the main report to support transparency and reproducibility. Raw proteomic data from ClusterVAP will be deposited in the PRIDE repository (ProteomeXchange) after publication. De-identified datasets may be shared on reasonable request, subject to approval by the relevant ethics committees and data transfer agreements.

### Strengths and limitations of this study

Multicentre design across five European countries enhances generalisability of findings.Use of bronchoalveolar lavage proteomics provides direct insight into local host response at the site of disease.Integration of molecular, clinical and microbiological data enables comprehensive characterisation of patient subgroups.Observational cross-sectional design precludes causal inference and limits assessment of temporal dynamics.Resource-intensive proteomic analysis may constrain scalability and external validation.

## Data Availability

Data sharing not applicable as no datasets generated and/or analysed for this study.
